#### 2.6.2. Secondary Outcomes

Parent and Child Outcomes:

All participants (intervention and control) will be asked to repeat the battery of measures completed at T1 to assess if there has been any change over time (within groups) and/or as a result of the Pathway Tool (between groups). Specifically, we will explore the direction and magnitude of any changes to (i) perceived self-efficacy in recognising and supporting flourishing in early childhood, (ii) perceived knowledge of how and when to seek support, (iii) engagement with and participation in supports relevant to flourishing in the early years, (iv) parent wellbeing, and (v) paediatric quality of life.

Data will be described for each available time point using frequencies and proportions for categorical data, medians and interquartile ranges for skewed data, and means and standard deviations for data that is normally distributed.

Outcomes will be analysed using mixed-effects regression models to account for repeated measures within participants. For continuous and Likert-scale outcomes, linear mixed-effects models will be used. In the presence of substantial skewness or deviation from model assumptions, alternative approaches such as mixed-effects quantile regression will be considered. For binary outcomes, generalised linear mixed-effects models with a binomial distribution and logit link function will be used. All models will include fixed effects for treatment group, time (baseline and follow-up), and their interaction, with a random intercept for participants. Models will be adjusted for the covariates used in the stratified randomisation, which include child age, gender, and locality, along with potential confounders, including socioeconomic status and mother’s age. Maternal age and socioeconomic status were included as covariates due to their established associations with both intervention engagement and outcomes related to parental wellbeing and child quality of life. Adjusting for these variables aimed to improve the precision of estimates and account for potential residual imbalance between groups.

When exploring these between-group differences, baseline values of the outcome will be included as covariates to allow adjustment for baseline score. Subgroup analysis by child age group will be conducted (0–2 and 3–5 years). We will report the precision of the model estimated by providing 95% confidence intervals. Missing outcome data will be handled under the assumption of missing at random using likelihood-based estimation inherent in mixed-effects models. Sensitivity analyses will be conducted to assess the robustness of findings, including analyses based on multiple imputation and complete-case analysis.

It has been previously acknowledged that the secondary outcome measures are considered exploratory data, with only small changes anticipated. Although statistical tests will be conducted, the focus will be on the direction and magnitude of change.

Sample Size:

We will aim to recruit N = 600 participants, with n = 400 randomly assigned to the intervention group and n = 200 to the control group. The primary acceptability endpoint is defined as the proportion of participants who rate all key acceptability items as ≥4. This outcome is therefore treated as a binomial proportion. The sample size was chosen to ensure adequate precision around the estimated proportion. Assuming an expected proportion of 60% (based on the predefined acceptability threshold), a sample size of 369 participants, which we rounded up to 400, yields a two-sided 95% confidence interval with a margin of error of approximately ±5%. Unequal allocation (2:1) was intentionally chosen to maximise the amount of information obtained on feasibility and acceptability outcomes in the intervention group, which is the primary focus of the study. The control group remains sufficiently sized to provide a comparator and to inform the design of a future definitive trial. While comparisons between groups will be conducted, these analyses will be considered exploratory, with emphasis placed on the direction and magnitude of effects rather than formal hypothesis testing. After allowing for a loss to follow up of approximately one third in each group, a total sample size of N = 400 would be available for follow-up analysis (intervention group n = 267 and control n = 133). Exploration of any differences between groups in perceived self-efficacy in recognising and supporting flourishing in early childhood and knowledge of programmes and resources, would allow for a small effect size (*d* = 0.30) to be detected using a Mann–Whitney U test, with a power of 80% and alpha of 0.05.

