## 2. Materials and Methods

### 2.1. Study Design

A randomised feasibility trial will be used to test the feasibility and acceptability of a new flourishing intervention and explore any areas for modification required (primary aim). A secondary aim will be to explore whether the intervention group shows any improvements in parent outcomes relative to controls after engaging with the Pathway Tool. This protocol is reported in accordance with SPIRIT guidelines and informed by the CONSORT extension for pilot and feasibility trials (see Section S2 of the Supplementary Materials) [40].

Participants will complete a screening form to determine eligibility and then be randomly allocated to either the intervention group (which will gain access the Pathway Tool immediately after completing the Flourishing Check), or the waitlist-control group (which will continue their usual activities and only gain access to the Pathway Tool after post-test assessments are completed or the final data collection time point has closed).

Quantitative and qualitative data will be collected at five timepoints: [T1] pre-intervention (baseline); [T2] acceptability and feasibility questionnaires (intervention group only), 1 week after T1; [T3] test–retest reliability (n = 200), 2–4 weeks after T1; [T4] qualitative feedback on the Flourishing Check and Pathway Tool (*n* ≈ 30, intervention group only), 3 months after T1; and [T5] post-intervention outcome measures, 6 months after T1. See Table 1 for a summary of the research procedure.

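### The secondary-outcome mixed model uses the baseline score as both response and covariate, so its group-by-time standard error is about 20% too small at the planned attrition

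*Protocol article*

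**What the plan says.** The protocol article, section 2.6.2 (Secondary Outcomes), specifies: "All models will include fixed effects for treatment group, time (baseline and follow-up), and their interaction, with a random intercept for participants". Baseline is a level of time, so each parent's baseline score is a response row. The section then adds, for the between-group comparison, that "baseline values of the outcome will be included as covariates to allow adjustment for baseline score". On missing data it says: "Missing outcome data will be handled under the assumption of missing at random using likelihood-based estimation inherent in mixed-effects models". Multiple imputation and complete-case analysis are named as sensitivity analyses.

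Each outcome has two occasions, T1 and T5 (section 2.1: "post-intervention outcome measures, 6 months after T1"). The Sample Size paragraph plans 400 against 200 parents and, "After allowing for a loss to follow up of approximately one third in each group", expects follow-up data on "intervention group n = 267 and control n = 133". The between-group analyses are called exploratory. Confidence intervals of 95% and tests are planned, with the focus on direction and magnitude.

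**The concern.** In the baseline row the response equals the covariate. Three things follow.

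- With complete data the covariate is constant within a parent and cancels from the group-by-time term. The estimate is the plain difference in change, and the intended baseline adjustment of that term does not happen.
- After conditioning on baseline, a parent's two residuals are negatively correlated. A random intercept can represent only zero or positive correlation, so its variance is estimated at zero and the repeated measures are no longer accounted for.
- Parents who drop out still contribute a baseline row, where the slope on the covariate is exactly 1. They pull the common slope away from its true value at follow-up, so the likelihood is mis-specified and cannot deliver the protection claimed for it.

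At stake are the precision, and under some dropout patterns the size, of the estimates that section 3 (Expected Results) wants for planning the effectiveness trial.

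**Working it through.** **The plan's own figure.** The plan states d = 0.30, 267 v 133, "with a power of 80% and alpha of 0.05". Taking a two-sided test, 0.30/√(1/267 + 1/133) = 2.83, and Φ(2.83 − 1.96) gives 80.7%. With the Mann-Whitney efficiency factor 3/π it is 78.9%. The stated 80% is reproduced and is not in question.

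**Inputs.** 400 v 200 randomised; fraction followed up f = 2/3 (or 1 for complete data). The correlation ρ between baseline and follow-up is not given for these outcomes. I assume 0.3 to 0.8; the only guide is the MHC-SF retest figure of 0.65-0.70 in section 2.3.3. SD is 1 at both times, and the other covariates are left out.

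**Common slope.** Pooling the baseline rows (slope 1) and the follow-up rows (slope ρ) gives c = (1 + fρ)/(1 + f). For f = 2/3 and ρ = 0.65, c = 1.433/1.667 = 0.86.

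**Random intercept.** The residual covariance within a parent is (1 − c)(ρ − c) = 0.14 × (−0.21) = −0.029. It is negative for every ρ < 1, because c always lies between ρ and 1. In simulated fits the intercept variance was zero every time for ρ from 0.3 to 0.8.

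**Standard error of group-by-time.** Let A = 1 − 2cρ + c² and D = (1 − c)². Apart from the common factor (1/400 + 1/200) = 0.0075:

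- variance reported by the model: D/f + A
- true variance: A/f + D − 2(1 − c)(ρ − c)

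For ρ = 0.65 and f = 2/3, A = 0.6216 and D = 0.0196.

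- Reported: 0.0294 + 0.6216 = 0.651, so SE = √(0.651 × 0.0075) = 0.070 SD.
- True: 0.9324 + 0.0196 + 0.0588 = 1.011, so SE = √(1.011 × 0.0075) = 0.087 SD.
- Ratio: √(0.651/1.011) = 0.80.

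| ρ | ratio, complete data | ratio, one third lost |
|---|---|---|
| 0.3 | 0.908 | 0.787 |
| 0.5 | 0.935 | 0.796 |
| 0.65 | 0.955 | 0.803 |
| 0.8 | 0.975 | 0.809 |

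The shortfall at one-third loss is 19-21% and hardly depends on ρ. A ratio of 0.80 turns the 1.96 cut-off into 1.57, a two-sided error of about 12%. Simulation gave 11-13%, with coverage of about 87-90%.

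**Bias.** Let m be the mean baseline score (in SD) of parents who stay, by arm. The group-by-time estimate is then off by (ρ − c)(m₁ − m₀).

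- Random loss: m₁ = m₀ = 0, so there is no bias.
- The same dependence on baseline in both arms: m₁ = m₀, so the treatment effect is unbiased. The within-group change is shifted by (ρ − c)m.
- Dependence in the intervention arm only: with log-odds of staying rising by 1 per SD and two thirds retained, m₁ is about 0.28. At ρ = 0.4, c is about 0.77 and the bias is −0.37 × 0.28 = −0.10. At ρ = 0.7, c is about 0.89 and the bias is −0.19 × 0.28 = −0.05. Simulation of this scenario gave 0.05-0.11 SD and false-positive rates of 20-29%.

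**Baseline used once.** On the same kind of data, three models had SE ratios of about 1.0, coverage of 93.5-96% and bias of about 0: the two-row model without the covariate, the same model with a common baseline mean, and follow-up ANCOVA. At ρ = 0.65 their SEs are 0.086, 0.081 and 0.081 SD.

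**The case against.** **A separate comparison may be meant.** Section 2.6.2 distinguishes within-group from between-group change and attaches the covariate only to the latter. If a follow-up-only ANCOVA was intended, the problem disappears. But the section gives every model a time effect with a baseline level, and nothing says that the baseline rows are dropped. With one row per parent, a random intercept could not be separated from residual error either. The text needs correcting on either reading.

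**The sensitivity analyses may catch it.** In part. Multiple imputation using arm and baseline removed the bias even under differential dropout, with coverage of 93-94%, so it would expose a discrepancy. It does not repair the main analysis. Complete-case analysis does not help: the covariate then cancels and the bias is (ρ − 1)m₁, about −0.17 at ρ = 0.4 and −0.10 at ρ = 0.65.

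**The outcomes are exploratory.** This stands and limits the severity. A reader might infer that the go/no-go decision or an efficacy claim is compromised. Table 3 rests on acceptability and feasibility proportions and focus groups, and the 400 was sized on the acceptability proportion. Nor does the plan make the intervals its main emphasis: it reports them for precision and focuses on direction and magnitude.

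**The missing-data point can be overread.** A reader might infer that any dropout biases the treatment effect. It does so only when dropout depends on baseline differently by arm. The protocol assumes about one third lost in each group and gives no figure suggesting such a pattern.

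**Conclusion.** The specification is wrong as written and should be fixed. At one-third attrition the group-by-time standard error is about 20% too small, with a false-positive rate of about 11-13% and coverage of about 87-90%. With complete data the shortfall is roughly 2-9%. The treatment estimate is unbiased under random loss or equal baseline-dependent loss. It is biased by about 0.05-0.11 SD in the differential-dropout scenarios tested, which is not negligible beside the d = 0.30 used for planning. Missing at random allows that kind of dropout, so the claimed protection does not hold for this model.

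The figures assume a linear model, normal outcomes, equal variances at both times and no other covariates. ρ is assumed, but the 20% is insensitive to it. The binary and quantile models share the duplicated baseline, but the size of the error there was not computed and these figures should not be carried over. The primary endpoint, its sample size and the stated power are unaffected.

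**What to change.** Use the baseline score once, by one of two routes.

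- Delete the sentence that adds baseline as a covariate. Keep the two-row mixed model with group-by-time as the effect, optionally with a common baseline mean across arms. This also keeps the within-group change that section 2.6.2 asks for.
- Or state that the between-group comparison is a separate follow-up-only ANCOVA: T5 score on group, baseline score, the stratification factors and the named covariates. This gives no within-group change, so the two-row model without the covariate would still be needed for that.

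Apply the same rule to the binary and quantile models. The cost is one or two sentences and no new data, and it is best done before the T5 data are analysed.

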Lastly, the Consumer and Community Advisory Committee strongly agreed that enforcing user registration may create a barrier to engagement with online content. Therefore, participants will not have to create a user account to engage with the Pathway Tool. This limits our ability to control who accesses the tool, as anyone who receives the URL can access it. Therefore, engagement metrics may be inflated by users who are not verified, participants. Additionally, control participants may gain access to the tool during the study. This will be partly mitigated by the URL being hidden from searches. Given the low-risk nature of the intervention and the study context, more intensive monitoring approaches (e.g., individual-level tracking, mandatory logins, or detailed analytics linkage) were considered disproportionate to the aims of the study and not feasible within available resources. Importantly, such approaches would also introduce additional privacy considerations and participant burden, which may further impact participation and engagement. Future research could implement stricter controls to more accurately assess the efficacy of the Pathway Tool.

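### The two named missing-data sensitivity analyses share the main model's missing-at-random assumption, so they cannot show how the exploratory 6-month group differences depend on it

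*Protocol article*

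**What the plan says.** Section 2.6.2 (Secondary Outcomes) sets the main approach: "Missing outcome data will be handled under the assumption of missing at random using likelihood-based estimation inherent in mixed-effects models". It follows directly with the robustness check: "Sensitivity analyses will be conducted to assess the robustness of findings, including analyses based on multiple imputation and complete-case analysis". The article names no analysis that departs from MAR, and it does not describe the multiple imputation as delta-adjusted or reference-based.

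The same section, under Sample Size, gives the scale of the loss: "After allowing for a loss to follow up of approximately one third in each group, a total sample size of N = 400 would be available". The split between the arms is given as "intervention group n = 267 and control n = 133".

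The models have two time points, baseline and follow-up, and adjust for the baseline score. Section 2.2.1 says the trial is unblinded. Section 4.1.2 says every measure except the engagement metrics is self-reported or proxy-reported, and that "more intensive monitoring approaches (e.g., individual-level tracking, mandatory logins, or detailed analytics linkage) were considered disproportionate to the aims of the study".

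Section 2.6.2 labels the between-group results exploratory and puts the weight on their direction and size. Section 3 says the measurements will feed effect-size estimates and the choice of outcomes for the next trial.

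**The concern.** A sensitivity analysis for missing data is useful when it changes the assumption that the main result depends on. Here the main model assumes that, given arm, baseline and covariates, parents who do not answer at T5 would have scored like those who do. Standard multiple imputation assumes the same. Complete-case analysis of a single follow-up, adjusted for baseline and the same covariates, needs very nearly the same condition. A parent with no T5 score adds almost nothing to the estimated group difference in any of the three.

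A departure from MAR is plausible in this design. Only one arm has the Pathway Tool before T5, parents know their allocation, and they report the outcomes themselves. Section 1.3 places engagement on the path to parenting change, so engagement could affect both the T5 score and whether T5 is completed. Individual use of the tool is not linked to participants and so cannot enter an imputation model.

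At stake are the direction and size of the T5 differences that the next trial would draw on. Three agreeing estimates could be reported as robust when the agreement carries little information.

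**Working it through.** **Inputs from the article (Section 2.6.2, Sample Size).** 400 and 200 randomised; about one third lost per group; planning effect d = 0.30; 80% power; alpha 0.05 (taken as two-sided, since sidedness is not stated).

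**Reproducing the article's figures.**
- Retained: 400 × 2/3 = 266.7 and 200 × 2/3 = 133.3, total 400, as stated.
- SE of d = √(1/267 + 1/133) = 0.106.
- Power for a comparison of means: Φ(0.30/0.1061 − 1.96) = Φ(0.867) = 80.7%.
- Mann–Whitney, scaling n by the asymptotic relative efficiency 3/π: 78.9%. Both are close to the stated 80%.

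**Precision at the planning effect.** Half-width = 1.96 × 0.1061 = 0.208, so an observed d of 0.30 has a 95% CI of 0.092 to 0.508. This ignores any gain from baseline and covariate adjustment.

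**Effect of a departure from MAR.** Let delta be the amount, in SD, by which unseen T5 scores fall below their MAR prediction. The documents give no value, so delta is an assumption. With one third missing in each arm:

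change in group difference = (1/3) × (delta in intervention − delta in control).

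With control delta = 0:

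| delta, intervention (SD) | change (SD) | d = 0.30 becomes |
|---|---|---|
| 0.1 | 0.03 | 0.27 |
| 0.2 | 0.07 | 0.23 |
| 0.3 | 0.10 | 0.20 |
| 0.5 | 0.17 | 0.13 |
| 0.9 | 0.30 | 0.00 |

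- The lower CI limit reaches zero at 0.092 ÷ (1/3) = 0.28 SD, holding the CI width fixed.
- The estimate reaches zero at 0.30 ÷ (1/3) = 0.90 SD.
- Equal deltas in both arms cancel.

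**Do the planned analyses agree when MAR fails?** A simulation used 400 + 200 participants, a true effect of 0 and a baseline–outcome correlation of 0.5. Controls were missing completely at random at 1/3. In the intervention arm, P(missing) = expit(−0.85 − 1.0 × y), so low scorers drop out more. Mean missingness was 32.9% (intervention) and 33.4% (control). Mean estimates, where the truth is 0:
- Mixed model: 0.21 SD (100 runs)
- Multiple imputation by arm: 0.22 SD (400 runs)
- Complete-case with baseline adjustment: 0.21 SD (400 runs)

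The three agree with each other and are all wrong by about 0.21/0.30 = 70% of the planning effect, despite nearly equal loss in the two arms. The dropout mechanism was built in and is strong: 0.214/0.329 implies a delta of about 0.65 SD. The simulation shows that agreement is uninformative. It does not estimate the bias in this trial.

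**The case against.** Several points on the other side stand.

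- **Open list.** The sentence on sensitivity analyses is not exhaustive, and an unseen SAP may add a further analysis. The point therefore does not rest on missing detail. It is that the two analyses the article names as its robustness check cannot serve that purpose for the assumption stated one sentence earlier.
- **Exploratory status.** The T5 comparisons are secondary and the article plays down formal testing. Table 3 bases progression on item ratings and focus groups, and no T5 group difference enters it. A reader might infer that the go/no-go decision is at risk; the documents do not support that.
- **MAR cannot be tested.** A reader might also conclude that the plan fails to test MAR. No analysis of the observed data could, including the one proposed here. What is missing is a view of how far the result moves under departures from MAR.
- **Complete-case analysis is not clearly stronger here.** With one follow-up and baseline plus covariates in the model, it stays valid when dropout depends only on those variables, which is close to the mixed model's own condition.
- **Auxiliary data exist.** Individual tool use is not linked, but parents' ratings of the tool are collected at T2 in the intervention arm and could inform the imputation. They help only partly: they exist in one arm, can be missing themselves, and are not a record of use.
- **Selective dropout is conjecture.** The article does not say who will miss T5, and it plans payment, reminders and save-and-return to limit loss.
- **Direction is fairly stable.** With d = 0.30 observed, even delta = 0.5 SD in one arm leaves 0.13 in the same direction.

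**Conclusion.** The point holds as a modest one about the exploratory T5 comparisons. The main analysis and both named sensitivity analyses rest on essentially the same MAR assumption, so their agreement would not show how direction and magnitude depend on it.

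The size depends on an assumed delta. With one third missing in the intervention arm and controls as predicted, 0.3 SD moves the estimate by 0.10 SD, a third of the planning effect. For an observed d of 0.30, the CI reaches zero at about 0.28 SD and the direction changes only beyond about 0.90 SD. If delta is similar in both arms, little or no bias follows.

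A reader might infer that the T5 results will be biased or that an apparent benefit would vanish. The documents do not support that: they give no information on who drops out, and it takes a large one-sided shift to remove the planning effect. The primary acceptability and feasibility outcome is untouched.

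**What to change.** Keep the MAR mixed model, the multiple imputation and the complete-case analysis. Add one delta-adjusted (pattern-mixture) multiple imputation for perceived self-efficacy and perceived knowledge of how and when to seek support:

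- Shift the imputed T5 scores by delta, varied separately in each arm, over a range wide enough to find the tipping point (beyond 0.90 SD if the observed d is 0.30).
- Use T2 ratings as auxiliary variables in the intervention arm where available.
- Report the delta at which the direction changes and the delta at which the CI reaches zero, together with T5 completion by arm.

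One added sentence in Section 2.6.2 would cover this. It builds on the imputation already planned and changes no data collection. The cost is a little more analysis and a range of estimates to report in place of a single figure.

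### The 80% power statement belongs to a Mann–Whitney test that the analysis section does not use, and the planned mixed model enters baseline twice, so its between-group contrast and detectable effect are unclear

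*Protocol article*

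**What the plan says.** All of this is in section 2.6.2 of the protocol article.

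- **Power.** Randomisation is 2:1, "with n = 400 randomly assigned to the intervention group and n = 200 to the control group". "After allowing for a loss to follow up of approximately one third in each group", the follow-up sample is "intervention group n = 267 and control n = 133". For self-efficacy and for knowledge of programmes and resources, this is said to allow an effect of d = 0.30 "to be detected using a Mann–Whitney U test, with a power of 80% and alpha of 0.05".
- **Model.** Continuous and Likert-scale outcomes go into linear mixed-effects models, with mixed-effects quantile regression as an example fallback for skewed data. "All models will include fixed effects for treatment group, time (baseline and follow-up), and their interaction, with a random intercept for participants".
- **Baseline.** For the between-group differences, "baseline values of the outcome will be included as covariates to allow adjustment for baseline score".
- **Missing data.** The main approach is likelihood-based estimation under missing at random. Complete-case analysis and multiple imputation are sensitivity analyses.
- **Status.** The group comparisons are called exploratory, with the focus on direction and magnitude. The sample size was set by the precision of the acceptability proportion.

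**The concern.** The article gives both a power figure and an analysis, and the two do not match. A Mann–Whitney comparison at T5 ignores baseline. In a model with baseline and follow-up as outcome rows, the group-by-time term is a difference in change, and its precision depends on the baseline to follow-up correlation r. In a baseline-adjusted comparison of T5 scores, precision depends on r in another way and is never worse than the unadjusted comparison. The text on the model points to the first contrast and the text on baseline covariates points to the second. Taken together they put baseline on both sides of the model.

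Two things are at stake. A reader cannot attach the stated d = 0.30 to the estimate that will be reported. And the 95% confidence intervals, which the plan offers as its measure of precision and which would inform the next trial, may be too narrow if the model is fitted literally.

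**Working it through.** **Inputs.** From section 2.6.2: N = 400 and 200 randomised, m = 267 and 133 followed up, d = 0.30, alpha 0.05 (two-sided assumed). Assumed: r, because none is given for the author-developed scales. Scores are standardised to SD 1, and power = Φ(d/SE − 1.96).

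**1. The plan's own figure.** Unadjusted SE = √(1/267 + 1/133) = 0.1061. The Mann–Whitney test has efficiency 3/π = 0.955 relative to the t-test for normal data, so its effective SE is 0.1061/√0.955 = 0.1086. Power = Φ(0.30/0.1086 − 1.96) = 78.9%, and a simulation of 20,000 trials gave 79.0%. The effect detectable at 80% power is (1.960 + 0.842) × 0.1086 = 0.304. Both round to the stated 80% and 0.30.

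**2. Contrast A: group-by-time interaction, likelihood analysis using all 600 baselines.** Variance per arm = (1 − r²)/m + (1 − r)²/N, summed over arms. At r = 0.3: 0.91/267 + 0.49/400 + 0.91/133 + 0.49/200 = 0.01393, so SE = 0.118 and power = Φ(0.30/0.118 − 1.96) = 72%.

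**3. Contrast B: T5 difference adjusted for baseline.** SE = 0.1061 × √(1 − r²). At r = 0.3 this is 0.1012, and power is 84%.

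| r (assumed) | A: interaction | B: baseline-adjusted T5 | Detectable d under B |
|---|---|---|---|
| 0 | 59% | 81% | 0.30 |
| 0.3 | 72% | 84% | 0.28 |
| 0.4 | 78% | 87% | 0.27 |
| 0.5 | 84% | 90% | 0.26 |
| 0.7 | 96% | 98% | 0.21 |

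Contrast A crosses 80% at r of about 0.44. The last column is 2.802 × 0.1061 × √(1 − r²).

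**4. The literal combination: baseline as outcome row and as covariate.** Write x for baseline and y for follow-up.

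- *Complete data.* The covariate has the same value in both rows of a participant, so it cancels from the interaction, which stays the difference in change. Its pooled coefficient is b = (1 + r)/2. The two residuals, (1 − b)x and y − bx, have covariance (1 − b)(r − b) = −(1 − r)²/4. This is negative, so the random-intercept variance goes to zero. The pooled residual variance is (1 − r)(3 + r)/4. The reported variance of the interaction is then (3 + r)/4 of the true one: 0.825 at r = 0.3 and 0.875 at r = 0.5. The type I error is 2 × (1 − Φ(1.96 × √0.825)) = 7.5%, and 6.7% at r = 0.5, against a nominal 5%.
- *One third lost at random.* Now b = (600 + 400r)/1000 = 0.72 at r = 0.3. The pooled residual variance is 0.6(1 − b)² + 0.4(1 − 2br + b²) = 0.4816. The reported SE is √(0.4816 × (1/400 + 1/267 + 1/200 + 1/133)) = 0.095. The true variance per arm is (1 − 2cr + c²)/m + e²/(N − m), with c = b + (1 − b)m/N and e = (1 − b)(N − m)/N, which gives a true SE of 0.121. The type I error is about 12%, and about 12% again at r = 0.5. Simulation of the zero-intercept fit (4,000 trials per setting) gave 12 to 13%.

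The true SE of 0.121 at r = 0.3 compares with 0.118 for contrast A and 0.101 for contrast B. The extra covariate therefore does not bring the gain of baseline adjustment.

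**The case against.** The strongest defence is that the power sentence is about differences between groups, and for those differences the plan says it will adjust for baseline. On that reading (contrast B) power is never below about 81%, and the Mann–Whitney figure is a cautious approximation. This stands as far as it goes: no shortfall is shown if contrast B is meant. It does not settle the matter, because the model text applies to all models and keeps baseline as a time point, and step 4 shows that the two instructions together do not yield contrast B.

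Three stronger readings might be inferred, and the documents support none of them.

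- *The 80% is miscalculated.* It is not: 78.9% and d = 0.304 round to the stated values.
- *Power falls to 67% at r = 0.3.* That is the interaction on completers only, with SE = 0.1061 × √(2(1 − r)). Complete-case analysis is a sensitivity analysis here; the planned likelihood analysis gives 72%.
- *The trial is underpowered.* The shortfall needs both the interaction reading and r below about 0.44. The only related figure in the article is a test–retest reliability of 0.65–0.70 for the MHC-SF, a different scale. At r = 0.65 the likelihood interaction has about 94% power. The comparisons are exploratory and did not determine N.

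A separate statistical analysis plan may name the contrast, but it could not make the published power sentence describe the published model.

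**Conclusion.** The point holds as a mismatch and a specification fault, not as an arithmetic error. The stated power is for an analysis that the plan does not contain. For the model as written it is unknown without r: about 72% to 84% over r = 0.3 to 0.5 if the interaction is the effect, and 81% or more if the baseline-adjusted T5 difference is. The more consequential part is the double use of baseline, which understates the standard error of the interaction: type I error of about 7% with complete data and about 12% with the expected one-third loss, for r of 0.3 to 0.5. These results assume normal scores of equal variance at both times, drop-out at random, a two-sided 5% level, and a random-intercept variance estimated at zero. Because the outcomes are secondary and exploratory, the correction is modest but worth making before analysis.

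**What to change.** 1. For the continuous and Likert-scale outcomes, define the treatment effect as the difference between groups at T5 adjusted for baseline. Use the baseline score once, as a covariate and not also as an outcome row, and keep the stratification factors and other covariates as planned.
2. Replace the Mann–Whitney sentence with the detectable effect for that model: with 267 v 133, two-sided alpha 0.05 and 80% power, about d = 0.28 at r = 0.3, 0.26 at r = 0.5 and 0.21 at r = 0.7. State that r is assumed.

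The cost is a reworded paragraph, and one stated figure becomes a range. The sample size, allocation and data collection do not change. With a single follow-up row per participant the random intercept is no longer needed for these outcomes, and drop-outs' baselines add little, so the handling of missing T5 scores should be restated to match; the multiple imputation already planned can serve.
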